## Abstract

**Background:**

The National Human Papillomavirus (HPV) Vaccination Program in Australia commenced in 2007 for females and in 2013 for males, using the quadrivalent HPV vaccine (HPV 6,11,16,18). Thus far, we have demonstrated very substantial reductions in genital warts and in the prevalence of HPV among young Australian women, providing early evidence for the success of this public health initiative. Australia has a long history of school-based vaccination programs for adolescents, with comparatively high coverage. However, it is not clear what factors promote success in a school vaccination program. The HPV.edu study aims to examine: 1) student knowledge about HPV vaccination; 2) psycho-social outcomes and 3) vaccination uptake.

**Methods/Design:**

HPV.edu is a cluster randomised trial of a complex intervention in schools aiming to recruit 40 schools with year-8 enrolments above 100 students (approximately 4400 students). The schools will be stratified by Government, Catholic, and Independent sectors and geographical location, with up to 20 schools recruited in each of two states, Western Australia (WA) and South Australia (SA), and randomly allocated to intervention or control (usual practice). Intervention schools will receive the complex intervention which includes an *adolescent intervention* (education and distraction); *a decisional support tool* for parents and adolescents and *logistical strategies* (consent form returns strategies, in-school mop-up vaccination and vaccination-day guidelines). Careful process evaluation including an embedded qualitative evaluation will be undertaken to explore in depth possible mechanisms for any observed effect of the intervention on primary and secondary outcomes.

**Discussion:**

This study is the first to evaluate the relative effectiveness of various strategies to promote best practice in school-based vaccination against HPV. The study aims to improve vaccination-related psychosocial outcomes, including adolescent knowledge and attitudes, decision-making involvement, self-efficacy, and to reduce fear and anxiety. The study also aims to improve school vaccination program logistics including reduction in time spent vaccinating adolescents and increased number of consent forms returned (regardless of decision). Less anxiety in adolescents will likely promote more efficient vaccination, which will be more acceptable to teachers, nurses and parents. Through these interventions, it is hoped that vaccination uptake will be increased.

**Trial registration:**

Australian and New Zealand Clinical Trials Registry, ACTRN12614000404628, 14.04.2014.

**Electronic supplementary material:**

The online version of this article (doi:10.1186/s12889-015-2168-5) contains supplementary material, which is available to authorized users.

## Background

With several countries having now implemented HPV vaccination programs, data on uptake are beginning to emerge. Although the age range for comparison varies internationally, there is a vast difference in HPV vaccine uptake across these countries, from very high—86.7 % for 3 doses in adolescent females of the target age in the UK (2013–2014) [1]—to very low—37 % for 3 doses among the adolescent age group in the US [2]. Uptake needs to be consistently high for a comprehensive reduction in HPV disease burden to be achieved at a population-level. In particular, if 3-dose vaccination coverage can be increased from 67 to 90 %, models predict that the long-term reduction in incident infection will be increased from 76 to 95 % [3]. In general, school-based programs tend to have higher coverage than non-school based programs [4].

The National HPV Vaccination Program in Australia commenced school delivery in April 2007 for girls and February 2013 for boys, using the quadrivalent HPV [qHPV] vaccine. The routine cohort for vaccination is age 11–14 years (year 7 or 8 in secondary school depending on jurisdiction). The HPV vaccine is offered alongside other vaccines in the national school vaccination program (e.g. Diphtheria, Tetanus and Pertussis (DTaP) booster and varicella vaccines). In Australia, the National HPV Vaccination Program Register reports that for girls aged 14–15 years of age (as of mid-2012), 82 % received HPV dose 1, 78 % received HPV dose 2, and 71 % received HPV dose 3 (2013) [5].

### Strategies for school-based vaccination

In Australia, a school-based delivery is used, and parental consent is required for the vaccination to proceed. Schools distribute parental consent forms (with an information brochure) to all eligible students to take home for signing.^1^ However, students most often receive little, or no, education about HPV or HPV vaccination prior to immunisation [6, 7] and there is no requirement for separate consent/assent from the adolescent. Perhaps implicit is an expectation that parents will discuss the vaccine and share information with their adolescent. Where adolescents are absent on a school vaccination day, or have not provided a signed consent form, they can access vaccination through a local immunisation clinic or their general practitioner.

There is little evidence available to guide strategies for school-based vaccination. Our systematic review of practices for school-based vaccination implementation identified only one randomised controlled trial in 14 studies, which evaluated process [8, 9]. We identified the importance of well-designed vaccination education to promote understanding, and strategies to promote return of consent forms and to vaccinate students absent on school vaccination days [10–12]. In addition, our qualitative research in Sydney schools highlighted the importance of procedural issues, as well as knowledge and attitudes, to vaccination consent and completion [13–15].

### Adolescents’ lack of knowledge and understanding about the HPV vaccine in Australia

There is now clear evidence that many adolescents have little or no understanding of the vaccines they receive or the diseases they are intended to prevent. Our research in Australian schools has shown that, adolescents’ understanding, self-efficacy, and involvement in decision-making regarding HPV vaccination are low, and that their fear and anxiety are high [6, 14, 15]. Further, even after widespread media promotion, participation in the consent process and experiencing vaccination, there was still a low level of knowledge among adolescents in Australia [6, 16, 17]; and even internationally despite high vaccination rates [18, 19]. Despite media awareness campaigns, there is also some uncertainty about where adolescents can and should obtain reliable information about the vaccine [6, 20].

### Adolescent experience of needle related anxiety with vaccination

We have previously described significant adolescent anxiety associated with HPV vaccination in the school-based setting [15, 21] from adolescent, parent and nurse reports as well as vaccination-day observations, and international studies reveal similar and related concerns [18, 22]. We identified a range of strategies from our previous research, including: education of students about HPV and HPV vaccination prior to vaccination day; vaccinating adolescents in the morning so that they are not waiting all day; use of privacy screens during vaccination; bringing adolescents to the vaccination area in small groups to avoid extended waiting times; having a separate entrance and exit point so that vaccinated adolescents do not have contact with those still waiting; distraction techniques such as iPod use while waiting for vaccination, and relaxation techniques such as breathing exercises learned prior to vaccination day, which may reduce vaccination related anxiety [13, 15, 21].

### Parent and adolescent HPV vaccination decision making

We previously described HPV vaccination decision-making by parents and adolescents in a school setting [14]. We identified that parents face challenges discussing HPV and vaccination with their adolescents, and adolescents rarely participate in decision-making [14]. This situation is not optimal for several reasons, including: the missed opportunity for adolescents and parents to effectively communicate about important health issues and to support adolescents developing autonomy; there are important ethical reasons why adolescents should participate in consent processes regarding their own health [7, 21, 23]. For the school-based vaccination context, there are currently no tools to support an informed decision-making process that can be shared between parents and adolescents.

In this paper we describe the protocol of our cluster randomised controlled evaluation of decisional support and logistical strategies in school-based Human Papillomavirus (HPV) Vaccination of adolescents.

## Trial aims

The study aims to examine: 1) student knowledge about HPV vaccination; 2) psycho-social outcomes and 3) vaccination uptake.

## Trial methods

### Study design

Cluster randomised controlled trial occurring over two school years: 2013 and 2014.

### Sample

The overall target sample is 40 schools with year-8 enrolments above 100 students, stratified by Government, Catholic, and Independent sectors and geographical location, with up to 20 schools recruited in each of two states, Western Australia (WA) and South Australia (SA).

### Setting

The greater metropolitan area of Perth, WA, and Adelaide, SA.

### Participants

Male and female students in their first year of high school (year 8 in participating states). Key school personnel in participating schools and immunisation nurses.

### Advisory board

An Advisory Board exists that includes representatives from the government, Catholic and Independent education authorities and from health department and immunisation teams in both study jurisdications. The purpose of this Advisory Board is to advise on all aspects of the study. The board will meet regularly prior to study initiation and during the study with email communication throughout.

### Ethics and informed consent

We obtained ethical approval from the Department of Health WA Human Research Ethics Committee and Women’s and Children’s Hospital (WCHN) Human Research Ethics Committee. Approval was also obtained from the relevant WA and SA government authorities. We sought approval for a consent waiver from parents for the evaluation of this study [24]. In Australia, Human Research Ethics Committees may grant consent waivers when: involvement in the research carries no more than low risk; the benefits from the research outweigh the risk of harm from not seeking consent; participants would be expected to consent if asked; confidentiality is maintained; and attempts to obtain consent are very unlikely to lead to adequate response rates. These conditions all held for this research project and, accordingly, the project was granted ethical approval [25].

### Randomisation

#### Permuted block randomisation

Schools will be stratified by state (WA or SA) and sector (Government, Independent single-sex, Independent coeducational, Catholic single-sex, Catholic co-educational) and within strata, randomised using permuted blocks. Randomisation lists will be created using the software program Rand.exe [26]. The researchers recruiting schools and the contact people at the schools will be blind to which arm of the trial the school will be allocated to at the time the school agrees to take part in the study. The trial statistician, who will have no involvement in recruitment, will allocate schools using the randomisation list after the school has agreed to take part. Schools will be allocated according to the list in the order in which they are recruited. Where possible, schools will not be allocated until the target number in the strata is reached. After the school is allocated, recruiters and schools will no longer be blind to intervention/control status.

### Intervention

The intervention consists of three main components: 1) an adolescent intervention; 2) an HPV vaccine parent/adolescent decision support tool; and 3) logistical strategies. The adolescent intervention is designed to promote knowledge, decision-making involvement and confidence in vaccination (self-efficacy) and reduce vaccination-related anxiety in adolescents. The *decisional support tool* is designed for use by both adolescents and parents together to promote understanding and shared decision-making. Logistical strategies are designed to improve vaccination uptake, school vaccination processes and the adolescent experience. The intervention components are outlined in further detail below:The *adolescent intervention* comprises: education taught through the school in an interactive lesson (see Additional file 1); a take-home magazine designed by and for adolescents; online components that can be accessed outside the school in a website and app for mobile devices; and distraction/relaxation methods to be used prior to and during vaccination, supported by nurses and teachers.Further information on the development of the adolescent intervention is detailed in a separate publication [27]. Briefly, education occurs via an 18 min animated film (on DVD) about HPV and HPV vaccination with seven chapters including: HPV- the virus; HPV vaccination; males and HPV; decision-making about HPV vaccination; what happens on the school vaccination day; cervical screening into the future. The film is designed to be screened in class, in an interactive way, with school personnel. A teacher user guide and supplement containing educational activities for each chapter accompany the DVD and other resources.The magazine includes a range of practical information about HPV and HPV vaccination, and the school vaccination day, in an appealing format. The magazine is designed to be taken home by students to read in their own time.A website (http://takechargehpv.org) and an app for mobile devices, including all educational resources will be available for students in intervention schools, to use in a flexible way. The website includes information about HPV and HPV vaccination and is intended to reinforce the information taught in class. Adolescents can re-watch the film clips, sign up to receive reminders about vaccination, and share their stories about being vaccinated.iPads will be available for use on vaccination day to assist with relaxation and distraction and will contain only the study app, which incorporates information from the website, the film chapters, the magazine, and relaxation exercises and distraction activities such as a painting tool.A HPV vaccination *decisional support tool* (DST) designed for use by both adolescents and parents together in the home environment is being used in the study. It has been developed using input from parents and adolescents [28]. We have an evidence-based decision aid, developed according to internationally accepted standards for presenting balanced information about health care options [29]. This was tested and refined after input from male and female adolescent-parent dyads obtained in interviews [28]. This decision aid also incorporates innovative methods to facilitate discussion of sensitive topics and shared decision-making.*Logistical strategies* will include methods for increasing consent form return such as direct mail-out of forms to parents (rather than being delivered to parents by adolescents); reminders (re-sending vaccination consent forms when they have not been returned); and non-material incentives for classroom consent form return (such as homeroom points) regardless of whether parental consent is granted. In addition, guidelines for nurses and teachers about the set-up of the vaccination room to minimise student anxiety, promote student privacy, and assist with the efficiency of vaccination processes (see Additional file 2), and distraction strategies to directly assist the management of adolescent anxiety will be implemented. In-school ‘mop-up’ vaccination for students who have a valid consent but were absent on a previous vaccination day will be provided both on standard vaccination days and through one additional visit per school after dose 3.

#### Training of staff to implement intervention

Prior to the commencement of the study in a school, study staff will offer training to school personnel in the educational and logistical components of the study. During this training a checklist of study activities will be provided to the coordinating staff member and discussed. A similar training session will also be completed with each of the school-based immunisation teams before the first vaccination day.

### Measure

#### HPV adolescent questionnaire (HAVIQ)

We have developed and validated a questionnaire (measure) to determine changes in adolescent knowledge, attitudes, fear and anxiety, self-efficacy, and decision-making [28]. The items in this measure have been informed by a review of existing questionnaires around HPV [30–34], the results of our own research [6, 7, 8, 13, 23], and an expert panel of academics working in related fields. The domains of the measure include: HPV and HPV vaccine knowledge and attitudes; HPV-related fear and anxiety ‘Feelings towards vaccination’; involvement in HPV vaccination decision-making; and HPV vaccination self-efficacy ‘Skills inventory’. Knowledge and attitudes, ‘Feelings towards vaccination’ and decision making involvement were measured with a series of questions (6, 6, and 8, respectively) each coded on a Likert scale (strongly agree to strongly disagree and scored 1–5); Skills inventory (5 questions) using a confidence scale from 0 to 100. The measure has been tested for face and content validity and internal consistency and test/re-test reliability. The questionnaire has been tested in six schools to determine preliminary impact on knowledge, vaccination self-efficacy and fear [35].

### Data collection

Psychosocial outcomes will be measured using the HPV Adolescent Vaccination Intervention Questionnaire (HAVIQ). School personnel will administer the entire HAVIQ questionnaire (all four domains) after the students have participated in the education intervention session, but before they have had dose 1 of the HPV vaccine in intervention schools, and prior to dose 1 in control schools. Both groups of schools will complete the ‘Skills inventory’ and ‘Feelings towards vaccination’ components of the questionnaire before dose 2 of the HPV vaccine to measure the change in these domains after personal experience with vaccination. The ‘Knowledge’ component of the questionnaire will be given again prior to dose 3 of the HPV vaccine to measure knowledge retention over time. Self-reported vaccination status will be included in the questionnaire prior to dose 3.

#### Vaccination uptake

We will obtain de-identified school-level immunisation uptake data from each State’s Health Department. De-identified student vaccination data will be linked to questionnaire data via codes generated by participating schools’ administration.

#### Time taken to immunise

This will be documented by the school-based immunisation nurses on the study “School-based Immunisation Log for Nursing Staff” on each vaccination day. The start and end time will be recorded, as well as the total number of hours/minutes spent vaccinating the students, excluding any breaks.

#### Standard procedures for vaccination in all schools

Consent for vaccination forms will be sent out as per normal operating procedures described in the relevant state guidelines. *Vaccination Room set*-*up*: Room set up to follow normal operating procedures described in relevant state guidelines. *Mop*-*ups*: To follow normal operating procedures described in relevant state guidelines.

### Statistical methods/analysis

#### Power calculation

To allow for the possibility of schools dropping out of the study, we increased the number of schools by 10 % and aimed to recruit a total of 40 schools. A total of 36 schools allows for the detection of a change in the percentage of students vaccinated from 70 to 80 % at a significance level of 0.05 and with a power of 80 % and assuming an intraclass correlation coefficient (ICC) of 0.05 [36]. We estimated the ICC from a pilot study in NSW to be 0.04, and other cluster trials of adolescent health behaviours have reported ICC’s of less than 0.05 [37]. We estimated, that on average, each school of the 36 schools would have 150 students giving a total final sample size of 5400 students.

With a total of 36 schools, we will be able to detect the following differences in means between the intervention and control groups for the four secondary outcomes: 1) Knowledge–minimum detectable difference “equals” = 0.7; 2) Fear/anxiety–minimum detectable difference “equals” = 0.7; 3) Decision making–minimum detectable difference “equals” = 0.5; 4) Skills inventory–minimum detectable difference “equals” = 18; all assuming an ICC of 0.05, power of 80 %, significance of 0.05 and standard deviations derived from a pilot study evaluating each of these measures and allowing for a 40 % non-completion of these outcomes [36, 37].

#### Primary outcome analysis

The primary analysis will compare vaccination rates using the Mantel-Haenszel method, taking into account the stratification by year, state and school sector and adjusted for clustering [36]. In addition, logistic regression models will be used to adjust for baseline vaccination rates (average of the previous 2 years), school type (single-sex, or mixed), school size and SEIFA index using generalized estimating equations (GEE) with robust standard errors. The level of implementation of the intervention will also be included.

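### The adjusted uptake model codes schools only as single-sex or mixed, so a foreseeable difference between boys' and girls' schools is left unadjusted, at some cost in precision

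*Protocol article*

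**What the plan says.** All places are in the Protocol article.

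- **Randomisation (Permuted block randomisation).** Schools are stratified by state and by "sector (Government, Independent single-sex, Independent coeducational, Catholic single-sex, Catholic co-educational", and are then "within strata, randomised using permuted blocks". Two states and five sector levels give ten strata. Four of them are single-sex: Independent and Catholic, in each state. None separates boys' from girls' schools.
- **Primary analysis (Primary outcome analysis).** A Mantel-Haenszel comparison of vaccination rates, "taking into account the stratification by year, state and school sector and adjusted for clustering".
- **Additional model (same section).** Logistic regression by GEE with robust standard errors, to "adjust for baseline vaccination rates (average of the previous 2 years", and for "school type (single-sex, or mixed), school size and SEIFA index". Level of implementation is also included. The school-sex term has two levels.
- **Who is enrolled (Participants).** "Male and female students in their first year of high school (year 8 in participating states".
- **Timing.** The Background says the national programme "commenced school delivery in April 2007 for girls and February 2013 for boys". Study design has the trial "occurring over two school years: 2013 and 2014".

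**The concern.** The trial covers years 1 and 2 of the boys' school programme and years 7 and 8 of the girls'. On these facts alone, sex is a foreseeable source of between-school difference in uptake. The plan includes a school-sex covariate but gives the two opposite kinds of school the same code. If boys' and girls' schools depart from mixed schools in opposite directions, one single-sex coefficient averages them towards zero. The single-sex versus co-educational split is also already built into the strata for the Independent and Catholic sectors. The covariate thus largely repeats a split that the design balances and omits one that it does not.

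A block in a single-sex stratum can put a girls' school in one arm and a boys' school in the other and still count as balanced. The realised arm difference may then partly reflect sex mix, and the adjusted model has no term to remove it.

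**Working it through.** **1. The plan's own figure.** Inputs from Power calculation: 70% versus 80%, significance level 0.05 (taken as two-sided), power 80%, ICC 0.05, 150 students per school.

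- Individually randomised size: 294 per arm.
- Design effect: 1 + 149 × 0.05 = 8.45.
- Schools per arm: 294 × 8.45 / 150 = 16.56. Adding one cluster per arm gives 17.56, rounded up to 18. The total is 36 schools and 36 × 150 = 5400 students, as stated.
- Standard error of the difference with 36 schools: sqrt[(0.70 × 0.30 + 0.80 × 0.20) × 8.45 / 2700] = sqrt(0.37 × 8.45 / 2700) = 0.034, or 3.4 points. With 40 schools, 3000 replaces 2700 and the result is 3.2 points.

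The sample size reproduces, and this point does not depend on it. The standard error serves only as a yardstick. It is the planning value for an unadjusted comparison, not that of the GEE model.

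**2. Does the baseline rate stand in for sex?** I take the baseline as HPV uptake and count the previous two years back from each cohort.

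| Cohort | Baseline years | Years with boys' school delivery |
|---|---|---|
| 2013 | 2011, 2012 | none |
| 2014 | 2012, 2013 | one (2013) |

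For 2013 an all-boys school has no comparable baseline, and a mixed school has a girls-only one. If both cohorts use the two years before the trial, neither baseline has boys' data. Either way, the covariate that would normally absorb school differences does not do so here.

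**3. Illustrative size.** The protocol gives no count of single-sex schools, no block size and no boys' uptake. Assume 40 equal schools, 20 per arm; one boys' and one girls' school in each of the four single-sex strata, split 1:1; 16 mixed schools per arm, half boys; and a boy-girl uptake gap of 5, 10 or 15 points.

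Let d be the number of boys' schools in the intervention arm minus the number in control. Each pair adds +1 or −1, so there are 2^4 = 16 equally likely allocations.

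| Absolute d | Probability | Share of boys by arm | Gap |
|---|---|---|---|
| 4 | 2/16 = 12.5% | (8 + 4)/20 = 60% vs 8/20 = 40% | 20 points |
| 2 | 8/16 = 50% | (8 + 3)/20 = 55% vs (8 + 1)/20 = 45% | 10 points |
| 0 | 6/16 = 37.5% | 50% vs 50% | 0 |

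SD of d = sqrt(4) = 2, so the SD of the gap in male share is 2/20 = 0.10. The shift in the arm difference is that gap times the uptake gap.

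| Assumed boy-girl gap | SD of shift | Shift at absolute d = 2 | Shift at absolute d = 4 |
|---|---|---|---|
| 5 points | 0.5 | 0.5 | 1.0 |
| 10 points | 1.0 | 1.0 | 2.0 |
| 15 points | 1.5 | 1.5 | 3.0 |

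With four schools per single-sex stratum, two of each sex, simulation gives a similar picture: absolute d is at least 2 in 65% of allocations, and the SD of the shift is about 0.6, 1.2 and 1.7 points.

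**4. Possible gain in precision.** If this component lies wholly inside the 3.4-point standard error, removing it leaves sqrt(3.4² − 0.5²) = 3.36, sqrt(3.4² − 1.0²) = 3.25 or sqrt(3.4² − 1.5²) = 3.05, a reduction of about 1%, 4% or 10%. Using 40 schools throughout (3.23 points), the remainders are sqrt(3.23² − 0.5²) = 3.19, sqrt(3.23² − 1.0²) = 3.07 and sqrt(3.23² − 1.5²) = 2.86, or about 1%, 5% and 11%.

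**The case against.** A reader might infer that the trial's effect estimate is biased by sex, or its test invalid. The protocol does not support that. Schools are randomised within the single-sex strata, so the imbalance is zero on average. Both analyses account for clustering, so between-school variation due to sex enters the standard error. Type I error is preserved when that is done properly.

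A reader might also infer that the primary result is at fault because of the quoted covariate. It is not: that covariate belongs to the additional model. The Mantel-Haenszel comparison does not use it and is not changed by recoding it.

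The size is also open to challenge. The Background gives uptake for girls only, and shows that the boys' programme is newer, not that boys' uptake differs. The pairs assumed above split the sexes across arms in every stratum. The 3-point shift needs both the largest assumed gap and an allocation with probability 12.5%. Few single-sex schools or a small gap would make the matter negligible. Nor is the extra parameter free in a model that already carries several school-level terms on 36 to 40 clusters.

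All of this stands and limits the point to precision and readability. It does not answer the coding itself. The two-level term is a stated choice, not a detail left to a fuller plan.

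**Conclusion.** The point holds as a modest improvement to the adjusted analysis. No stratum or listed covariate separates boys' from girls' schools during the boys' first two programme years, and the baseline rate does not make up for it. The consequence is some lost precision and an estimate that may partly reflect the realised sex mix. It is neither bias on average nor a false error rate. Under the stated assumptions the shift is typically a small fraction of the standard error and of the 10-point target, and the gain in precision is roughly 1% to 10%. These sizes depend on an assumed number of single-sex schools and an assumed sex gap, neither of which the protocol gives.

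**What to change.** In Primary outcome analysis, replace the two-level school type in the GEE model with three levels: all-boys, all-girls and co-educational. Alternatively, use student sex if the linked student data described under Vaccination uptake carry it; the protocol does not say whether they do.

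The three-level factor needs only what is known about every school, so no new data are required. It costs one extra parameter with about 36 to 40 clusters. Fixing it before the results are seen is more credible than adding it after an imbalance appears.

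No change to allocation is proposed. Blocking boys' and girls' schools separately would raise the strata from 10 to 14, under three schools each (40/14 = 2.9), and reordering schools by sex would conflict with the rule that they are allocated in order of recruitment.

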#### Secondary outcome analysis

Mean change in scores of knowledge, self-efficacy, fear/anxiety, and decision-making will be compared between groups using two-sample t-tests with appropriate adjustment for clustering. Baseline scores for knowledge will be taken from the control group. Proportion of consent form returns will be compared between groups prior to dose 1 using Chi-square test with appropriate adjustment for clustering. Time taken to vaccinate will be measured by nurses during each immunisation day in both intervention and control schools. It will be calculated as the mean time to vaccinate 50 students in intervention schools compared with control schools. Mean time to vaccinate will be compared between groups in both years of the study to determine effect of the intervention over time. We will investigate whether the intervention improves vaccination rates through its effect on fear reduction, and self-efficacy increase, by comparing estimates of the effect of the intervention both with and without adjustment for the possible intermediary variables of fear/anxiety, and self-efficacy. These logistic regression models will use GEE and robust standard errors to account for the clustering.

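### The additional covariate-adjusted GEE for uptake will give p-values and intervals that are too optimistic with 36 to 40 schools unless its robust variance is corrected for small samples

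*Protocol article*

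**What the plan says.** Under Primary outcome analysis the article names the main test: "The primary analysis will compare vaccination rates using the Mantel-Haenszel method", stratified and adjusted for clustering. It then introduces, as an addition, logistic models that "adjust for baseline vaccination rates (average of the previous 2 years), school type (single-sex, or mixed), school size and SEIFA index", fitted "using generalized estimating equations (GEE) with robust standard errors". A further term follows: "The level of implementation of the intervention will also be included".

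Under Secondary outcome analysis the models that examine fear/anxiety and self-efficacy as intermediaries use the same machinery: "These logistic regression models will use GEE and robust standard errors to account for the clustering".

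The number of independent units comes from Power calculation: "A total of 36 schools allows for the detection of a change in the percentage of students vaccinated from 70 to 80" per cent. For dropout, "we increased the number of schools by 10 % and aimed to recruit a total of 40 schools". Neither analysis section says whether the robust variance is corrected for the number of schools, or which reference distribution is used.

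**The concern.** The sandwich variance is justified by a large number of clusters, not of students. The planned 5400 students form only 36 schools. Arm is a school-level variable, and so, as naturally measured, are baseline uptake, school type, school size and SEIFA. Each fitted school-level term pulls the fitted values towards the observed school rates. The squared residuals that feed the sandwich then become too small and the standard error is biased downwards. A normal reference adds to the error, because it ignores that the variance is itself estimated from few schools.

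This is the uptake model that adjusts for schools' previous uptake. Readers may lean on it if chance imbalance between arms makes it differ from the Mantel-Haenszel result. Its p-values and intervals should therefore mean what they say.

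**Working it through.** **1. Number of schools.** Inputs from Power calculation: 70% against 80%, alpha 0.05 (taken as two-sided), power 80%, ICC 0.05, 150 students per school.
- Individually randomised size per arm: [1.96·√(2·0.75·0.25) + 0.842·√(0.70·0.30 + 0.80·0.20)]² / 0.10² = 293.2, so 294.
- Design effect: 1 + 149·0.05 = 8.45. Students per arm: 294·8.45 = 2484. Schools per arm: 2484/150 = 16.56; adding one cluster per arm gives 17.56, so 18.
- Total 36; 36·1.1 = 39.6, so 40.

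The plan's figures reproduce, so K = 36 to 40 is the right basis.

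**2. Rough size by hand.** With p parameters the average leverage of a school is p/K, and the uncorrected standard error is too small by about √(1 − p/K). Intercept, arm and four covariates give p = 6.
- K = 36: √(1 − 6/36) = 0.913. The effective cut-off is 1.96·0.913 = 1.789, and the two-sided tail of t with 30 df is 8.4%.
- K = 40: √(1 − 6/40) = 0.922. The cut-off is 1.807, and the tail of t with 34 df is 8.0%.
- Arm only (p = 2): 6.5% at K = 36 and 6.4% at K = 40, by the same steps.

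This ignores uneven leverage and the extra variability of the sandwich, so somewhat higher simulated rates are expected.

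**3. Simulation under no effect.** Logistic GEE with school as cluster, uptake 70%, ICC 0.05, mean 150 students. Working correlation was exchangeable, or independence in some runs; there were 4,000 or 10,000 trials per setting. Assumed, because the article does not give them: 1:1 allocation, two-sided Wald test, school-size coefficient of variation 0.4, and the covariate distributions. In some runs baseline uptake explained half the between-school variance. Rejection rates at nominal 5%:

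| Model and variance | 36 schools | 40 schools |
|---|---|---|
| Arm only, uncorrected, z | 6.5–6.9% | 6.0–7.1% |
| Arm + four covariates, uncorrected, z | 8.9–10.4% | 8.2–9.1% |
| Same, uncorrected, t(K − p) | 7.8–9.3% | 7.1–8.0% |
| Same, Kauermann-Carroll, t(K − p) | 5.4–6.3% | 5.1–5.6% |
| Same, Mancl-DeRouen, z | 4.1–4.5% | 4.1–4.5% |

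Monte Carlo standard error is about 0.3 to 0.5 points. Multiplying the variance by K/(K − 1) removes at most 0.5 points. Adding level of implementation as a fifth term (10,000-trial runs) gives 9.5–9.6% at 36 schools and 8.9–9.0% at 40. Separately written simulations of the four-covariate model gave 8.4% to 10.1% at 36 schools and 8.7% to 9.4% at 40.

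**4. Sensitivity** (36 schools, four covariates, uncorrected z): ICC 0.04, 9.4%; ICC 0.10, 8.4%; uptake 80%, 8.7%; equal school sizes, 9.0%; coefficient of variation 0.6, 8.0%; 110 students per school, 8.5%.

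**5. Mediation models.** The adjusters named are student-level scores, and no school-level covariate is listed. A null simulation had 2,000 trials, independence working correlation, ICC 0.05, 60% completion and two student-level covariates with an assumed ICC of 0.05. It gave 7.1% at 36 schools and 7.5% at 40 (Monte Carlo standard error about 0.6 points).

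**The case against.** The best objection is that the finding rests on silence. Bias-corrected sandwiches are also robust standard errors, so the wording is compatible with the fix. The variance correction and the reference distribution are details that a condensed article can leave to an analysis plan, which is not shown here. This stands in part: that the uncorrected form will be used is an inference, and the figures above are conditional on it. It does not dispose of the point. The article fixes the estimator, the clusters and the covariates, and that method followed in its plain default form is anti-conservative.

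Three stronger readings are tempting and are not supported.
- A reader might infer that the trial's main conclusion carries this inflation, since the text stands under Primary outcome analysis. The GEE is an addition; the primary test is the cluster-adjusted Mantel-Haenszel comparison, for which no inflation has been shown.
- A reader might infer that false positives nearly double in the mediation models too. Those list no school-level covariates, and the simulated rate is about 7%.
- A reader might add the design strata to the GEE and quote a larger error. The article assigns state, sector and year to the Mantel-Haenszel analysis, and its GEE school type has two levels.

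Nor does the problem call for replacing the covariates by strata plus baseline uptake. State (1 parameter), five-level sector (4) and baseline (1) make six parameters, more than the four now named.

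**Conclusion.** The point holds for the additional adjusted uptake model. If the uncorrected sandwich is used with a normal reference, a nominal 5% test rejects in about 8 to 10% of null trials, and a nominal 95% interval covers about 90 to 92%. Most of the excess comes from the four school-level covariates; with arm alone the rate is about 6 to 7%. The direction is secure, and the size was stable over the ICCs, uptake levels and school-size patterns tried. It still rests on simulation with assumed allocation, sidedness, school-size spread and covariate distributions. Because the model is supplementary, this is something the sponsor should correct and not a flaw in the primary test.

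**What to change.** State that every GEE model under Primary outcome analysis and Secondary outcome analysis uses a small-sample corrected robust variance, for example Kauermann-Carroll, with a t reference on the number of schools minus the number of model parameters. With the four named covariates that is 36 − 6 = 30 or 40 − 6 = 34 degrees of freedom. A t reference alone is not enough. The covariate list need not change for this purpose.

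The cost is a sentence and a software option, with no new data. Intervals become somewhat wider: by the hand approximation, about 2.042/1.789 = 1.14 times at 36 schools and 2.032/1.807 = 1.12 times at 40.
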